## Abstract

**Background:** There is consistent evidence that community and clinical samples of individuals with an alcohol use disorder (AUD) have attentional biases toward alcohol cues. The alcohol attentional control training program (AACTP) has shown promise for retraining these biases and decreasing alcohol consumption in community samples of excessive drinkers. However, there is a lack of evidence regarding the effectiveness of ACTP in clinical AUD samples. The main aim of the present study is to investigate whether primary pharmacological and psychological, evidence-based alcohol treatment can be enhanced by the addition of a gamified AACTP smartphone application for patients with an AUD.

**Design and Methods:** The study will be implemented as a randomized controlled trial. A total of 317 consecutively enrolled patients with AUD will be recruited from alcohol outpatient clinics in Denmark. Patients will be randomized to one of three groups upon initiation of primary alcohol treatment: Group A: a gamified AACTP smartphone application + treatment as usual (TAU); Group B: a gamified AACTP sham-control application + TAU; or Group C: only TAU. Treatment outcomes will be assessed at baseline, post-treatment, and at 3- and 6-month follow-ups. Repeated measures MANOVA will be used to compare the trajectories of the groups over time on alcohol attentional bias, alcohol craving, and drinking reductions. It is hypothesized that Group A will achieve better treatment outcomes than either Group B or Group C.

**Perspectives:** Because attentional bias for alcohol cues is proportional to the amount of alcohol consumed, and these biases are not addressed within current evidence-based treatment programs, this study is expected to provide new evidence regarding the effectiveness of the gamified AACTP in a clinical population. Furthermore, due to promising results found using AACTP in community samples of excessive drinkers, there is a high probability that the AACTP treatment in this study will also be effective, thereby allowing AACTP to be readily implemented in clinical settings. Finally, we expect that this study will increase the effectiveness of evidence-based AUD treatment and introduce a new, low-cost gamified treatment targeting patients with an AUD. Overall, this study is likely to have an impact at the scientific, clinical, and societal levels.

**Clinical Trial Registration:**
https://clinicaltrials.gov/ct2/show/NCT05102942?term=NCT05102942&draw=2&rank=1, identifier: NCT05102942.

## Background

Alcohol-use disorder (AUD), as defined by DSM-5 criteria, is very common in the Western world, with a 12-month prevalence of 14% and a lifetime prevalence of 29% (1). Furthermore, AUD is the most prevalent and most harmful of all substance-use disorders (2, 3) and is among the leading causes of illness, disability, and mortality (4, 5). The high prevalence and severity of AUD underscore the importance of having easily available and effective treatments.

Overall, evidence-based psychological treatments, such as cognitive-behavioral therapy (CBT), have shown to be effective in the short term (6). During CBT, patients with an AUD are taught methods to help them identify high-risk situations for relapse. They also learn coping strategies for avoiding alcohol in high-risk situations. Patients are, however, supposed to learn these strategies by applying explicit and controlled cognitive techniques rather than practicing the strategies while being exposed to alcohol *in vivo* (7–9). Recovering patients often experience a relapse when they are exposed to alcohol and related stimuli in real-life, and they can only later analyze the consequences of their behavior. Patients with an AUD initially respond well to evidence-based psychological treatments, but as many as 50% of them relapse within 6 months after treatment discharge (10–12). This indicates that CBT and other evidence-based psychological treatments do not address all the crucial cognitive dysfunctions associated with maintaining an addiction; thus, they may not prepare patients to deal with their inevitable confrontation with alcohol cues in real life in Western societies.

One shortcoming of current psychological treatments is that they mainly target explicit and controlled cognitive dysfunctions. However, according to dual process models of addictive behaviors, confrontation with alcohol cues *in vivo* is influenced by two semi-independent cognitive systems: (1) a fast associative *impulsive* system, which is involved in the automatic evaluation of alcohol-related stimuli in the environment in terms of their emotional and motivational significance and which initiates approach or avoidance responses; and (2) a slow and controlled *reflective* system, which is involved in the regulation of the automatic and implicit responses elicited by the impulsive system, and which is responsible for explicit and controlled, higher-order cognitive processes (13–16).

Addictive behaviors, such as AUD, can be conceptualized as a dysfunction of these systems, whereby an over-activated impulsive system becomes sensitized and triggers approach behaviors toward alcohol cues, whereas a relatively under-activated reflective system is unable to regulate the behavior. Because the impulsive system is partly automatic and implicit, approach behaviors targeting alcohol cues in the environment allow the self-destructive drinking behavior to be maintained, even though the drinker might have explicit knowledge about the consequences generated by the reflective system (15, 16). Corroborating evidence from functional neuroimaging studies suggest that patients with AUD exhibit aberrant activation in dorsolateral prefrontal cortex, insular cortex, and anterior cingulate cortex, which are structures that act as a critical part of the reflective system (17–21). In addition to the of hypoactivation of the neural correlates for the reflective system, hyperactivation of subcortical structures such as ventral striatum and nucleus accumbens have also been found in AUD, which underlines the notion of a dysfunctional interaction between the reflective and impulsive systems (19–22). Although standard evidence-based psychological treatments for AUD target and attempt to modify dysfunctions in one of the cognitive systems that influence the maintenance of an AUD, the impulsive cognitive dysfunctions are addressed to a much lesser extent.

A cognitive dysfunction in the impulsive system that has consistently been identified as a crucial component in the maintenance of an AUD is alcohol attentional bias (AB). An AB for alcohol cues refers to the implicit and automatic cognitive process of selectively focusing attention on alcohol-related stimuli in the environment at the expense of processing other relevant stimuli (23, 24). AB for alcohol cues has been measured by using a variety of experimental paradigms (25). Among the most widely used paradigm is the alcohol variant of the experimental Stroop task (24, 26, 27). The alcohol Stroop consists of two categories of stimuli: alcohol-related (e.g., beer, wine, tavern) and neutral (e.g., chair, envelop, juice). During the task participants are asked to name the color (i.e., red, yellow, blue, or green) in which each stimulus appears as fast and accurately as possible while ignoring their content and meaning. The degree of AB is indicated by slower mean reaction times to alcohol cues compared to neutral cues and is calculated as an interference score. The alcohol-related meaning of the stimuli is presumably either capturing the person's attention more readily or maintaining the attentional focus for a longer period of time than the neutral cues (24). AB as measured by the alcohol Stroop task has consistently been found in both community and clinical samples of excessive drinkers (28–31), and the degree of AB is proportional to the amount of alcohol that participants habitually consume (24). For example, clinical AUD samples exhibit greater AB than sub-clinical samples of heavy drinkers (24, 29, 32). In addition, the degree of AB is inversely related to drinkers' ability to control their drinking (31, 33–35). Finally, it has been shown that clinical samples of AUD patients who have stronger alcohol AB at treatment admission are more likely to have an unsuccessful treatment outcome compared to patients with less AB, and the degree of AB of the unsuccessful patients increased during the course of treatment, suggesting that abstinence increases attentional awareness of alcohol cues (28). Taken together, the research suggests that AB is of utmost importance in maintaining an AUD and if not corrected, it might impede the effectiveness of other treatments and cause the patient to relapse.

The principles underlying the experimental alcohol Stroop task have recently been applied in the Alcohol Attention Control Training Program (AACTP), which is a computerized training program aimed at increasing drinkers' cognitive control over their alcohol AB. As illustrated in Figure 1, the AACTP consists of three different levels of training.

**Figure 1 F1:**
[figure not shown]
Alcohol attention control training program: In Level 1, neutral or alcohol stimuli are successively presented on the screen, while the colored background of the screen needs to be identified. In Level 2, instead of the background, a colored outline needs to be identified. In Level 3, neutral and alcohol stimuli appear simultaneously of which the neutral stimulus needs to be identified.

At Level 1, individual pictorial stimuli with a colored background (e.g., red, or green) are shown one at a time on a computer screen. Each stimulus is either alcohol-related or neutral. The participant is instructed to ignore the content of the stimuli while naming the color of the background. At Level 2, again an alcohol-related and a neutral stimulus is presented successively on the computer screen one at a time. In contrast to Level 1 in which the pictures have a colored background, the pictures now have only a colored outline whose color the participant is supposed to identify, thus making the task more difficult than at Level 1. At Level 3, two stimuli (an alcohol-related one and a neutral one) are presented simultaneously on the computer screen. The participant is asked to identify as quickly and accurately as possible the outline color of the neutral stimulus, while ignoring the alcohol-related stimulus.

The AACTP uses a variety of pictorial alcohol-related stimuli to train participants to progressively divert their attention away from alcohol-stimuli, with increasing levels of difficulty across the training. The alcohol AACTP has been evaluated in community samples of excessive drinkers who have shown reductions in both AB and alcohol consumption at post-treatment and follow-up (32, 36, 37). Recent reviews and meta-analyses do point to methodological shortcomings and conflicting evidence on the effects of training programs targeting AB across patients with various addictive disorders, including AUD (38–40). Despite the need for more well-designed studies, there is, however, also evidence suggesting that AACTP may be more promising for targeting alcohol consumption when compared to other AB training programs (40). Furthermore, the ACTP has been studied as an add-on treatment among clinical populations with food- and opiate addictions. In both cases, the addition of the ACTP in the experimental group led to a greater reduction in disease-specific AB and the accompanying unhealthy behavior than in the control groups (41, 42). This evidence suggests that AACTP might be a promising tool for ameliorating AB in clinical samples of patients with an AUD, especially when used in conjunction with a conventional treatment for AUDs.

In contrast to many other psychological treatments, clinical neuropsychological treatments building on experimental laboratory tasks are particularly suitable for alternative delivery pathways, such as tablets and mobile applications. These delivery pathways make it possible to use gamification elements, which would increase patients' motivation to participate. Gamification is defined as the use of game-design features in a non-gaming context, such as in a psychological treatment setting. Gamification would make the intervention more engaging, enjoyable, and motivating for participants (43), and using gamification elements is likely to enhance compliance with neuropsychological treatments. Commonly used gaming techniques include time-pressure, sound effects, feedback, progression in level of difficulty, achievement rankings, and competition (43–45). Although the AACTP have shown great promise in treating cognitive dysfunctions not targeted by conventional psychological treatments, the use of gamification elements may enhance compliance with and the effectiveness of these interventions.

Taken together, the results of prior studies are promising in terms of the clinical relevance of AB training. However, the small number of studies with small sample sizes conducted to date highlights the need for future research to verify the robustness of these mostly positive findings in actual clinical AUD settings (40). Further, adding gamification elements may increase compliance and hence the effectiveness of the intervention.

### Aims

The main aim of the study is to determine whether a gamified version of the AACTP when used as an add-on to a primary evidence-based treatment will increase the treatment's effectiveness. Based on the available evidence, it is hypothesized that the experimental group (Group A) will achieve a better treatment outcome than either the active control group (Group B) or the treatment-as-usual group (Group C). Additionally, we hypothesize that there will be a dose-response effect in Group A: the more that the patients use the AACTP, the better their outcome will be. Full descriptions of the experimental and control groups are provided in Section 2.5 below.

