### Experimental and Control Groups

The 317 patients (see power analysis below) fulfilling the eligibility criteria will be randomized to one of the three groups: Group A: AACTP delivered *via* a smartphone application + treatment as usual (TAU; *n* = 106), Group B: ACTP sham training delivered *via* a smartphone application + TAU (*n* = 106), or Group C: TAU only (*n* = 106). Patients in Group A will receive seven sessions of AACTP (one session per week for 7 weeks). Patients in Group B will receive seven sessions of sham training (one session per week for 7 weeks). Patients in Group C will receive only the primary treatment for AUD. Patients in the AACTP and sham control groups will start the primary treatment within the 1st month of their admission, so that the add-on treatment will not extend beyond the 3-month treatment period.

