#### Attentional Control Training Program Sham Training *via* a Smartphone Application

The AACTP sham control training is like the AACTP in that it is delivered *via* a smartphone application based on an Android or iOS application and is designed in accordance with the conventional program. Patients receiving the sham control program will also have the application installed on their personal smartphone. They, therefore, will be able to use the program in any location that they wish. However, different from the AACTP, patients in the active control group will be trained to direct their attention toward the non-alcohol-related stimuli on only 50% of the trials. On the remaining trials, their attention will be directed toward the alcohol-related stimuli. Thus, the sham training should counteract the induction of AB with AB re-training because the allocation of the participant's attention will distribute equally between the alcohol-related and the non-alcohol-related stimuli. The patient will respond by touching the circle displayed on the computer screen as quickly and accurately as possible. Like the ACTP training, a red outline will signal a stimulus that should be ignored, and a green outline will signal a neutral stimulus, which should be responded to, but the alcoholic or non-alcoholic stimuli will appear equally often with the red or green outline. Also, throughout each session, the speed at which the stimuli are presented will systematically increase, and the width of the outlines will decrease and gradually fade away in the final sessions, thereby increasing the difficulty of the task. In case the patient makes an error and touches an incorrect stimulus, the tablet will provide an auditory-visual alert. As in the smartphone version of the alcohol ACTP, prior to each session the participant will be encouraged to set a goal for the speed of the reaction times and the number of errors made until his or her performance plateau has been reached. After completing each session, the patient will be given both graphical and auditory feedback. Hence, the program will contain all the same features as the smartphone version of the alcohol ACTP. The only difference is that the patient's attention will be equally guided toward non-alcohol-related and alcohol-related stimuli in the sham control version. Selected practice data will be sent to the server to control for dose-response effects. Having the sham condition is important for ensuring that effects obtained with the smartphone version of the alcohol ACTP result from the re-training of the patients' alcohol attentional bias and not from the additional attention that they receive or from some other unintended effect, such as the Hawthorne effect (53).

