A power analysis (79, 80) was conducted using G^*^Power for a repeated-measures MANOVA with α = 0.05; effect size (ES) of *f* =0.20; power = 0.90; groups *k* = 3; and time-points measurements = 4. It showed that 88 participants will be required for the final analyses in each of the four cells (total *N* = 264). Prior evaluations identified *f* s of 0.30 (AB) and 0.37 (weekly mean drinking) and an *f* of 0.42 (situational confidence to resist drinking) on outcome measures for sub-clinical excessive drinkers (36). Further, in a study that used the intervention as an add-on treatment for clinical participants with a substance-use disorders other than AUD, effect sizes of *f* s = 0.33 (drug-specific AB), 0.34 (number of relapses), 0.32 (temptation to use) and 0.37 (self-confidence to resist temptation) were identified (42). Also, an unpublished study conducted with detoxified drug-abusers found *f* s of 0.39 (drug-specific AB), 0.18 (number of relapses), and 0.35 (temptation to use) (81). A second power analysis for a MANOVA with special effects and interactions was conducted to test the dosage-effect across groups (α = 0.05; EF *f*
^2^(*v*) = 0.06; power = 0.90; *k* = 3; predictors = 3; and response variables = 8), which yielded an *N* of 220. Attrition in similar studies has usually ranged from 10 to 15% (41, 42). Assuming a somewhat higher attrition rate (20%), which is not unlikely (82, 83), indicates that 317 (264 + [264·0.20]) participants should be tested at baseline for an analysis using listwise deletion of missing cases, although a multiple imputation (MI) analysis will also be conducted to verify that results converge across missing data assumptions. The projected sample size is sufficient for the planned data analyses, including mediational analyses based on Fitz and MacKinnon's guidelines (84).

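### The dose-response hypothesis concerns Group A alone, but the only dosage power figure (0.90, N = 220) is for an effect across three groups, so the stated hypothesis is not powered and its within-arm association is open to adherence bias

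*Protocol article*

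**What the plan says.** The Aims section adds a second hypothesis to the main comparison: "there will be a dose-response effect in Group A: the more that the patients use the AACTP, the better their outcome will be". It is confined to Group A and worded as an effect of use on outcome.

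The Statistical Analysis section describes no dose analysis among its methods. Dose appears there only in the sample-size paragraph: "A second power analysis for a MANOVA with special effects and interactions was conducted to test the dosage-effect across groups". The listed inputs are α = 0.05, f²(V) = 0.06, power 0.90, k = 3, and "predictors = 3; and response variables = 8", with a resulting N of 220. The paragraph ends by calling the projected sample sufficient for the planned analyses.

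Under Experimental and Control Groups, each arm has 106 patients. Groups A and B are both scheduled for seven weekly sessions, and "Patients in Group C will receive only the primary treatment for AUD". Training is done on the patient's own phone, at home if wished. For the sham arm the protocol adds: "Selected practice data will be sent to the server to control for dose-response effects".

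**The concern.** Two things do not fit together. First, the hypothesis is about variation in use inside one arm, while the power statement is about an effect across three arms, one of which has no use to vary. A reader who meets 0.90 in the sample-size paragraph will take it to cover the dose-response hypothesis, because no other dosage calculation is given.

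Second, everyone in Group A is scheduled for the same seven sessions, so differences in dose arise mainly from non-adherence after randomisation. Patients who keep training may also be those who are more motivated, drinking less or still in treatment. An association of use with outcome can then appear without any training effect, and the causal wording under Aims invites its reading as efficacy. A null result would be just as hard to read, because the test has too few patients.

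**Working it through.** **Inputs.** From Statistical Analysis: α = 0.05, f² = 0.06, target power 0.90, k = 3 groups, q = 3 predictors, p = 8 responses, N = 220, loss 20% with listwise deletion (multiple imputation as a check). From Experimental and Control Groups: 106 per arm.

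**1. The plan's own figure.** For a special-effects MANOVA (Pillai), s = min(p, q) = 3, df1 = pq = 24 and df2 = s(N − k − p + s) = 3(N − 8). The noncentrality is λ = f²·s·N (O'Brien-Shieh) or λ = f²·df2 (Muller-Peterson).

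| N | df2 | λ (two forms) | power |
|---|---|---|---|
| 162 | 462 | 29.2 / 27.7 | 0.90 / 0.88 |
| 170 | 486 | 30.6 / 29.2 | 0.92 / 0.90 |
| 220 | 636 | 39.6 / 38.2 | 0.98 / 0.97 |

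The smallest N for 0.90 is 162 or 170 (167 with a Wilks version), not 220. A value near 220 needs a changed input, such as two predictors (217) or f² = 0.045 (221). The document states neither.

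**2. Who has a dose.**
- Groups A + B randomised: 106 + 106 = 212; after 20% loss, 212 × 0.8 = 169.6, about 170.
- Group A randomised: 106; after loss, 106 × 0.8 = 84.8, about 85.
- Group C: none.

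**3. Power within Group A at f² = 0.06.** This assumes that the plan's multivariate effect size can be carried over to a within-arm slope; f² = 0.06 corresponds to r = √(0.06/1.06) = 0.24.

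One outcome, one dose predictor: df1 = 1, df2 = n − 2, λ = 0.06n.
- n = 85: λ = 5.10, power 0.61.
- n = 106 (all patients kept, optimistic): λ = 6.36, power 0.70.
- 0.90 requires n = 178. With 85 patients it requires f² of about 0.127 (r about 0.34).

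Eight outcomes, one dose predictor: df1 = 8, df2 = n − 9.
- n = 85: 0.25 to 0.27.
- n = 106: 0.32 to 0.35.

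**4. Power of the arm by sessions interaction.** Assume 85 per arm, the f² = 0.06 slope in A, a zero slope in the sham arm and equal residual variance. The variance of a difference of two slopes is twice that of one if sessions vary equally in both arms, so λ = 5.10/2 = 2.55 on 1 and 166 df, and power is 0.36. If the variance of sessions in the sham arm is 20% lower, λ = 5.10/(1 + 1/0.8) = 2.27 and power is about 0.32.

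**5. Adherence bias, illustration only.** The document gives no correlations. Suppose that there is no training effect and that motivation correlates c with both use and outcome. The spurious correlation is c². For c = 0.3, 0.4 and 0.5 it is 0.09, 0.16 and 0.25, and by Fisher's z a two-sided 5% test at n = 85 rejects in about 13%, 31% and 64% of trials. These rates show direction and sensitivity, not an estimate for this trial.

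**The case against.** The protocol can be defended on several counts, and parts of the defence stand.

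- A reader might infer that 0.90 power is claimed for a test within Group A. It is not: the figure belongs to a calculation that "was conducted to test the dosage-effect across groups". The defect is a mismatch of hypothesis and calculation, not a false claim about a within-A test.
- A reader might also infer that removing Group C destroys the stated power. On the listed inputs the roughly 170 app users left after loss still reach 0.90 to 0.92 for that MANOVA. But this is an omnibus test of three unnamed predictors on eight responses. Its 170 is not a power basis for a slope in one arm or for an interaction.
- It is tempting to put the listed MANOVA inputs through at n = 85 and report power of about one half (0.48 to 0.54). That carries three groups and three predictors into a one-arm test. The one-predictor figures above are the relevant ones.
- The article does not say that dose will be analysed only within Group A. Logging sham practice data to control for dose-response suggests that the sham arm may be meant as comparator, and the model could properly sit in an analysis plan not shown. This stands, so the absence of a model is not the criticism. An analysis plan cannot, however, make the two sections agree or enlarge Group A.
- Calling use self-selected would go too far: the schedule is fixed and the app can control the number of sessions per period. Patients can still miss sessions, which is why non-adherence is the likely source of variation.

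**Conclusion.** The point holds as a mismatch with a consequence for interpretation. The Group A hypothesis has no power calculation of its own, and the dosage calculation that is given concerns a different test and does not reproduce (about 162 to 170 against 220). None of the within-A tests examined reaches 0.90 at f² = 0.06: one outcome gives 0.61 to 0.70, and eight outcomes less. These values rest on carrying the plan's effect size over to a within-arm slope and on its 20% loss.

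That dose is not randomised follows from the design. That motivation or retention biases the association is plausible, but its size is unknown. The randomised comparison of weekly mean drinking, the primary outcome, is not affected, so this should be corrected but does not threaten the main result.

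**What to change.** - Reconcile Aims with Statistical Analysis, so that the dose-response hypothesis and its power statement describe the same test.
- Define that test as the arm (A vs B) by sessions-completed interaction on weekly mean drinking, using the practice data from both apps. State its assumption: adherence relates to outcome similarly in the two arms. If it does not, the comparison does not remove the bias.
- Report the slope within Group A as exploratory, without causal wording.
- Withdraw 0.90 and N = 220 as support for the Group A hypothesis, correct or explain the inputs behind 220, and state power for the test used: about 0.61 for a one-outcome slope in 85 patients, or about 0.32 to 0.36 for the interaction at 85 per arm if the sham slope is zero.

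The cost is a change of wording and a recalculation, since practice data are already to be sent to the server from both apps. The real price is power: the interaction is weaker than the within-arm slope, so the dose-response question should be presented as one that this trial can inform but is unlikely to settle.
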